### Recruitment {15}

Enrolment of patients in eliPfad will occur within two working days after admission to an internal ward if the eligibility criteria are met. To achieve efficient recruitment at each site, investigators at participating hospitals will form collaborations with other internistic departments and the emergency ward within their sites, allowing automated identification of suitable patients under privacy regulations. Close patient support will be provided by a case manager who will coordinate the transition from inpatient to outpatient care, assist the patient in implementing the specific elements of eliPfad, and serve as the primary point of contact for the patient during eliPfad. Case managers have been trained as nurses (3 years in Germany) and have worked in this role in a hospital for several years. In addition, they have advanced training as a case manager with additional training specific to eliPfad (certified by the “Deutsche Gesellschaft für Care und Case Management” (German Association for Care and Case Management, DGCC)). This training program comprises 216 h of courses including 3 days of supervision and 150 h of self-study. The case manager at each site routinely receives daily information on the admission of appropriate patients by implementing adequate arrangements for IT-based identification of patients at each hospital. In addition, direct recruitment occurs through the participating wards in each center, which are specifically contacted and queried by the case manager on all business days. The case manager verifies that patients meet or do not meet the inclusion and exclusion criteria and also assesses the MPI for this purpose. Patients who meet all criteria and wish to participate in the trial will be informed about the study by the investigator, including an information pamphlet. Written informed consent is obtained. Primarily, patients of the collaborating health insurance companies are recruited, but patients of other health insurance companies can also be included in eliPfad under a treatment contract.

## Assignment of interventions: allocation

### Sequence generation {16a}

Sequence generation is performed by the electronic data capture system (EDC, secuTrial®), which also provides the electronic case report form (eCRF). The software’s own “Extended Stratified Block without List” is used here, which represents a stratified block randomization. Factors for stratification are center and sex. Because of the 6 centers, there will therefore be 12 strata.

### Concealment mechanism {16b}

The allocation of the patient to the intervention or control group is done by secuTrial® (see above). Only after the inclusion of the patient and fulfillment of all inclusion and exclusion criteria, the patient can be randomized. Since the randomization is done without a list as mentioned above, the allocation can in no way be known before the randomization. Allocation concealment is therefore guaranteed.

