### Eligibility criteria {10}

The inclusion criteria are:Emergency hospital admission or transfer to a normal internal medicine ward in the form of:Direct admission from home / the referring GPAdmission from the emergency departmentTransfer from another hospital (reason for admission: internal medicine)Transfer from another ward within the hospital with initial admission due to an internal diseaseAge ≥55 yearsMultimorbidity (presence of at least 3 long-term health conditions)At least one of the following index diagnoses:Heart failure (NYHA I-IV)Chronic kidney disease (CKD)Chronic obstructive pulmonary disease (COPD)Diabetes mellitus (DM)Peripheral artery disease (PAD)Coronary heart disease (CHD)Arterial hypertension (AH)High risk of unplanned readmission (risk assessment by Multidimensional Prognostic Index (MPI) ≥0.34)Written informed consent, documented by signature, after sufficient reflection period. Patient-informed consent cannot be obtained during a medical emergency

The exclusion criteria are:Patients admitted to the hospital due to a non-internal disease (this includes the reason for initial admission to the referring hospital)Patients likely to be released from hospital within 2 working daysResidents of nursing facilities, home-based 24-h care, predominantly bedridden patientsLack of rehabilitation potential according to the attending physician’s assessmentInsufficient command of German language among patients and relatives/friendsA higher degree of visual and/or hearing impairment, if no relatives availableDiseases with a life expectancy of less than 6 monthsDesired rehabilitation on days 1 to 42 after discharge from index hospitalizationTravel distance from participating hospital to patient’s home 50 km or more (exceptions based on individual decision are possible) Patients with full private health insurance Patients who are in a dependent/employed relationship with the investigators Lack of capacity to consent Placement in an institution by court or official order

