### Implementation {16c}

Potentially eligible patients are screened. This verifies that patients meet the inclusion and none of the exclusion criteria. This is performed by the study physician and study nurse. If all criteria are met, the study physician will inform the patient. Once the patient has given informed consent to participate in the study, their data is entered into the eCRF (hosted by secuTrial®). Subsequently, secuTrial® also carries out the randomization, and the study team is directly informed in which group the patient will participate in eliPfad.

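### The absence of a randomisation list prevents look-up, not inference: with 1:1 blocks within center and sex in an open-label trial, the guarantee of allocation concealment does not follow

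*Protocol article*

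**What the plan says.** All references are to the protocol article.

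- **Sequence generation {16a}.** The EDC system uses a block routine without a stored list, "which represents a stratified block randomization. Factors for stratification are center and sex". On the number of strata: "Because of the 6 centers, there will therefore be 12 strata". No block size is given, nor whether it is fixed, varied or withheld from sites.
- **Concealment mechanism {16b}.** A patient can be randomised only after inclusion and confirmed eligibility. From the absence of a list it concludes that "the allocation can in no way be known before the randomization. Allocation concealment is therefore guaranteed".
- **Implementation {16c}.** Screening is done by the study physician and study nurse. Consent, eCRF entry and randomisation follow, after which "the study team is directly informed in which group the patient will participate in eliPfad".
- **Recruitment {15}.** Here the screener is a different person: "The case manager verifies that patients meet or do not meet the inclusion and exclusion criteria and also assesses the MPI for this purpose". The case manager also delivers the intervention.
- **Eligibility criteria {10}.** Some entry criteria involve judgement, such as rehabilitation potential and likely early release. For the 50 km travel limit, "exceptions based on individual decision are possible".
- **Trial design {8}** states open label and 1:1. **Composition of the coordinating center and trial steering committee {5d}** gives each center other than Cologne one study physician, one case manager and one study nurse. Cologne has two study physicians. Each center's team meets daily.

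**The concern.** Two different routes lead to advance knowledge of an allocation. One is to look the sequence up; having no list closes it. The other is to work out the next assignment from those already made, because a balanced block restricts what can still come. The second route needs only the block restriction and a record of past allocations in the stratum, and both are present here whether or not a list exists.

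At stake is selection at entry. Someone who expects a particular arm next can, without intending it, bring a patient forward, hold one back, or grant or refuse a discretionary exception. Covariate adjustment cannot be relied on to remove the resulting imbalance in unmeasured prognosis. Participants and assessors are unblinded (Who will be blinded {17a}), so concealment is the main protection at this stage. A reader who accepts the guarantee would see no reason to check whether it held.

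**Working it through.** **Inputs.** Ratio 1:1 ({8}); blocks within center and sex ({16a}); 948 randomised (Sample size {14}); allocations disclosed at once ({16c}). Block size is an assumption throughout.

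**1. The plan's own figure.** 6 centers × 2 sexes = 12 strata, as stated. The average is 948/12 = 79 patients per stratum, an average only, since recruitment need not be equal. Study setting {9} counts 5 centers with 6 hospitals, which would give 10 strata. That should be tidied but does not affect what follows.

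**2. Fixed block size known to staff.** For block size b = 2m at 1:1:

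- Share of allocations that are certain because one arm is already full in the block: 1/(m+1).
- Correct-guess rate when always guessing the arm that is behind, with a coin toss when level: [m + (4^m / C(2m,m) − 1)/2] / (2m).

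For b = 4 (m = 2): certain share 1/3 = 33.3%; guess rate [2 + (16/6 − 1)/2]/4 = 2.833/4 = 70.8%.

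| Block size | Certain | Correct guess |
|---|---|---|
| 2 | 50.0% | 75.0% |
| 4 | 33.3% | 70.8% |
| 6 | 25.0% | 68.3% |
| 8 | 20.0% | 66.6% |
| 10 | 16.7% | 65.3% |
| 12 | 14.3% | 64.3% |

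Full enumeration of all balanced blocks gives the same values.

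**3. Block sizes varying at random.** Strata of 79 were simulated with each size equally likely. An allocation counts as certain when the running imbalance has reached half the largest possible size.

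| Sizes | Certain from imbalance alone | Correct guess |
|---|---|---|
| 2, 4 | 5.5% | 71.9% |
| 4, 6 | 1.0% | 69.0% |
| 2, 4, 6 | 0.8% | 70.0% |
| 4, 6, 8 | 0.2% | 67.8% |

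This counting rule is narrower than the one in step 2. Applied to a fixed block of 4 it gives 8.5%, not 33.3%, because it ignores block boundaries. An observer who knows the set of possible sizes and uses the whole history does better. For sizes 2 and 4, two like allocations at the start of a block show that it is a block of 4, and the next two are then certain. The chance per block is 1/2 × 2/6 = 1/6, and the mean block length is 3, so the certain share is 2 × (1/6)/3 = 11.1%. The imbalance rule catches only the first of the two: (1/6)/3 = 5.6%, in line with the simulated 5.5%. Tracking every block size compatible with the history in the other three schemes gave about 5.4%, 4.0% and 2.4%. So the certain share is about 0.2% to 5.5% on imbalance alone and about 2% to 11% for a full-history observer. The guess rates do not change.

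**4. Who knows and who decides.** {15} puts the eligibility check and MPI scoring with the case manager; {16c} puts screening with the study physician and study nurse. Under either reading, screening lies with the team that is told every allocation. Both stratum factors are known before randomisation.

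**The case against.** The strongest reply is that the size of the problem rests on a block scheme the article does not give. An article may properly withhold block size, and its absence is no error. The routine's name does not show that its blocks are fixed. This stands. A reader might infer from the fixed-block table that many allocations, somewhere between 190 and 474 of 948, were knowable in advance. The document does not support that, because those counts need one fixed size that staff know or have worked out.

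Existing safeguards also deserve credit. Randomisation is electronic and follows consent and eligibility entry. Candidates are found through IT-based identification and ward queries on every business day, and enrolment must occur within two working days of admission, so deferral is limited. Rehabilitation potential is judged by the attending physician. The exclusion for desired rehabilitation rests on the patient's own statement (Relevant concomitant care {11d}), so it is not a staff judgement. These points narrow the room for selection but do not close it, because the choice of whom to bring forward comes before eCRF entry.

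Better-than-chance guessing is a property of blocking in general, and varying the sizes barely lowers it. That is correct, and it is also why the absolute claim fails: no block scheme tested brings the rate down to 50%. Finally, the two screening passages can be read as successive steps, with the case manager pre-checking and the physician and nurse confirming. The article does not say so.

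**Conclusion.** The point holds as an incorrect statement about a key safeguard. No list means no look-up; it does not mean that the allocation cannot be inferred. Under every scheme tested with sizes up to 8, a screener who tracks the local sequence guesses the next arm correctly in about 67% to 75% of cases, and in 64% even with a fixed block of 12. Certain knowledge ranges from 50% to 20% with fixed, known blocks of 2 to 8. With randomly varying sizes it is about 0.2% to 5.5% on imbalance alone, or about 2% to 11% with full bookkeeping. These figures assume that past allocations in the stratum are tracked; the certain shares also assume knowledge of the fixed size, the largest size or the set of sizes, as the case may be. Which scheme applies cannot be determined from the article.

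A reader might go further and infer that selection took place or that central randomisation was unsound. Nothing in the document shows either. The correction should be made, but sample size, alpha and the planned analysis are untouched.

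**What to change.** 1. In {16b}, withdraw both absolute claims. Say that the sequence cannot be looked up, and that some allocations may nevertheless be inferred from earlier ones in the stratum.
2. For any patients still to be randomised, ensure that secuTrial uses randomly varying block sizes not disclosed to sites. If this is already so, state that sizes vary and are withheld, without giving them. Recruitment was planned to run to 08/31/2025 (Trial status); if it has closed, this item lapses and the others remain.
3. Reconcile {15} with {16c} so that one named role makes and records the final eligibility decision, including discretionary items and exceptions to the 50 km limit, before randomisation opens.
4. Add a baseline check. For each patient, derive the arm that is behind from earlier assignments in the stratum, and compare MPI and age between patients for whom intervention and control were the predictable arm. A systematic difference would point to selection. Table 1 places the MPI at enrolment, before allocation.

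Cost: a wording amendment, possibly one EDC setting, and a little extra analysis; no additional patients. Varying the blocks allows slightly larger arm imbalance within a stratum. It mainly removes certainty and lowers the guess rate only slightly, so items 3 and 4 are needed as well.

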### Implementation {16c}

Potentially eligible patients are screened. This verifies that patients meet the inclusion and none of the exclusion criteria. This is performed by the study physician and study nurse. If all criteria are met, the study physician will inform the patient. Once the patient has given informed consent to participate in the study, their data is entered into the eCRF (hosted by secuTrial®). Subsequently, secuTrial® also carries out the randomization, and the study team is directly informed in which group the patient will participate in eliPfad.

## Assignment of interventions: blinding

### Who will be blinded {17a}

Blinding of the participants is impossible given the kind of intervention of this trial. Assessors will not be blinded either, because patients in the intervention group will be in possession of the tablet and the medical devices. During the hospital stay, these items will be in close proximity of the patient and difficult to hide. At A2 it is the assessor’s task to take these items back to the study center after the assessment. Therefore, they need to know which patient is in which group. However, observer bias is not estimated to be a big problem, because all questionnaires are either filled in by the patient directly or require answers that need no interpretation by the assessor such as number of drugs prescribed or weight loss. Nevertheless, to minimize observer bias, all assessors are specially trained. All evaluators will be blinded.

### Procedure for unblinding if needed {17b}

The design is open label with only outcome assessors being blinded so unblinding will not occur.

## Data collection and management

### Plans for assessment and collection of outcomes {18a}

Data for the primary outcome—the number of rehospitalizations 6 months after the discharge from the index hospital stay—will be cleaned from the data provided by the collaborating statutory health insurance companies. The quality of the data provided can be assumed to be high and the data to be complete. Specification of the dataset to be delivered by the health insurance companies will be determined beforehand. Data will be delivered at two time points by the health insurance companies. Data will be cleaned and quality assured. The secondary outcomes will be collected by the case manager or a study nurse during visits to the patient’s home. Most of the secondary outcomes will be assessed using questionnaires. These questionnaires have been validated and produce reliable results and are therefore scientifically accepted.

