### Outcomes {12}

#### Time points, data collection, and outcomes

Four time points (T) are defined which are accompanied by timely scheduled assessments (A). All assessments are carried out by members of the study team in person to ensure the completeness of the data. Pretests of the single questionnaires and the entire data collection assessment were conducted to test duration and feasibility for the patient population. Depending on the visit, these assessments are carried out either in hospital or at the patient’s home:T0/A0: Baseline, immediately after randomization and up to 2 working days after admission to the internal ward (in the hospital).T1: Discharge day from the index hospital stay. A1 can be performed up to 3 days before scheduled discharge (in the hospital) or up to 3 days after T1 (in the patient’s home).T2: End of the intervention phase, 42 days after T1. A2 can be performed up to 5 working days after T2 (in the patient’s home); if A2 cannot take place in this period (hospital admissions, etc.), A2 can still be collected on day 60 at the most, counted from discharge from the index hospitalization.T3: 180 days after T1. A3 can be performed up to 10 working days after T3 (in the patient’s home).

The primary outcome is the number of unplanned rehospitalizations over 180 days after the end of the index hospital stay. Unplanned inpatient readmission is defined as the admission of a previously discharged patient due to unplanned events or deterioration of health that can no longer be treated in the outpatient setting. The rehospitalization frequencies are determined using collaborating health insurance companies’ data. In addition, at A3, the patients are actively questioned by the case manager about possible hospital stays in the last 180 days.

The secondary outcomes are the variables required for the testing of the secondary hypotheses. The variables collected, when they are collected and the type of source are listed below:

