The following data will be obtained by A2 at the latest:Duration of index hospital stayDuration of stays in intensive or intermediate care units during the index hospital stayDuration of stays in other departments within the index hospital stay, if these departments are not part of the local eliPfad teamTransfers to external hospitals including geriatric facilitiesLength of stays in external hospitals including geriatric facilities after the index hospital stayTransfers to rehabilitation facilitiesDuration of stays in rehabilitation facilities

The following data are collected using collaborating statutory health insurance companies’ data at A3:Frequency and type of use of services in outpatient and inpatient care, drug prescription, remedies, and aids between T1 and T3Number of rehabilitation services between T1 and T3Number of transfers to “acute” geriatric units between T1 and T3Length of stay in inpatient facilities (incl. hospitals and rehabilitation facilities)Death between T1 and T3The sum of costs based on the above-defined service areas of collaborating health insurance companies’ data between T1 and T3

The following data will be collected by questioning the participants (if necessary, the relatives, the treating physicians) at all survey points (A0–A3):Quality of life using EQ-5D-5LDepression using the Geriatric Depression Scale (GDL)Geriatric assessment using the Multidimensional Prognostic Index (MPI)Timed up and go Test (TUG)De Morton Mobility Index (DEMMI)Minimal Nutritional AssessmentHealth status using the Self-Rated Health QuestionnaireSelf-efficacy (General Self-Efficacy Short Scale, ASKU)Medication planHealth literacyThe personal treatment burden

The following data will be collected at the survey points A0, A2, and A3:Patient-centeredness of care using PACIC

The following data will be collected at A1, A2, and A3:

Questioning about personal therapy goals / self-management

The following data are recorded at A2 and A3:Actual number of drugs taken by the patient at home using photo documentation

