Two principal investigators (PIs) represent the coordinating center on the steering committee and are responsible for conducting the study at the University Hospital Cologne. In addition, there is a project coordinator who assists in the implementation of the PIs’ decisions and acts as an interface between all professional groups of the coordinating center. Two study physicians are responsible for the daily implementation of the study at the University Hospital Cologne site. They obtain informed consent from suitable patients, develop the treatment plan together with the case manager, and communicate primarily with the physicians in the outpatient area. Furthermore, a case manager is responsible for the patients at the University Hospital Cologne site. She supports the patients in using the tablet and medical devices, draws up the treatment plan and is the primary contact for patients. She also conducts the weekly video calls with the patient after discharge from the index hospital stay. A study nurse is also employed to carry out the patient assessments, enter the data into the database and check it for completeness. Finally, a study nurse carries out the cross-center monitoring but is not otherwise involved in the implementation of the study. At each of the other centers, 1 study physician, 1 case manager, and 1 study nurse are employed for the tasks described above. The members of each center involved in the day-to-day study activities meet once a day to coordinate the day and assign tasks. Each center has hired its own employees and works independently.

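### The case manager who delivers eliPfad may also assess its secondary outcomes, and the protocol contradicts itself on who assesses and whether assessors are blinded

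*Protocol article*

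**What the plan says.** **Who assesses.** Section {18a} of the protocol article states: "The secondary outcomes will be collected by the case manager or a study nurse during visits". Under Intervention description {11a}, the case manager returns at the end of the six weeks for the final assessment and takes back the equipment. Under Outcomes {12}, at A3 "the patients are actively questioned by the case manager about possible hospital stays in the last 180 days". The section on the coordinating center and steering committee {5d} differs: "A study nurse is also employed to carry out the patient assessments". It adds that each of the other centres has one study nurse for the same tasks.

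**Who is blinded.** Section {17a} says "Assessors will not be blinded either, because patients in the intervention group will be in possession of the tablet and the medical devices", and separately that evaluators are blinded. Section {17b} says "The design is open label with only outcome assessors being blinded so unblinding will not occur".

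**Why observer bias is discounted.** Section {17a} argues that "all questionnaires are either filled in by the patient directly or require answers that need no interpretation by the assessor", and adds that assessors are specially trained.

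**The concern.** The case manager is not a neutral data collector. Section {11a} makes this person the coordinator of eliPfad and the patient's standing contact, who visits in the first week at home, checks vital parameters twice weekly and makes weekly video calls. If the same person then administers PACIC, treatment burden, self-efficacy and EQ-5D-5L, intervention patients report on their care to the person who gave it. Control patients have no such relationship with whoever asks them. Courtesy in the answers would then differ by arm. Training assessors does not remove this, because it arises on the patient's side.

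The blinding contradiction matters separately. A reader judging detection bias would reach opposite conclusions from {17a} and {17b}.

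**Working it through.** No figure in the protocol is at issue, so the check sets the sections side by side.

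**1. Is the case manager really an assessor, or is this only a loose 'or' in {18a}?**
- {11a}: the case manager makes the final visit at six weeks and collects the tablet and devices.
- {17a}: taking these items back at A2 is the assessor's job. Together, these make the case manager the A2 assessor in the intervention arm.
- {11b}: the case manager's later home visits fall at 42 days (+5 working days) and 180 days (+10 working days). {12} gives A2 and A3 exactly these days and windows.
- {12}: the case manager asks the hospital-stay question at A3.
- {5d}: the study nurse does the assessments.

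Four sections point to the case manager, as assessor or possible assessor, and one to the nurse. The role is stated inconsistently, which is more than a detail left open for the SAP.

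**2. Can {17a} and {17b} both be true?** No. {17a} says assessors are unblinded and, at A2, must know the group. {17b} says outcome assessors are the one blinded party. {17a} treats evaluators as a separate, blinded group, so {17b} probably means them, but it does not say so.

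**3. How far does the argument against observer bias reach?** It is limited to questionnaires and to interpretation by the assessor.
- Not covered, staff-administered measures: {12} lists the MPI, Timed up and go and DEMMI. Table 1 labels the MPI a geriatric assessment and has a row for mobility tests. {12} has all assessments carried out in person by the study team.
- Not covered, response bias: a self-completed or purely factual item can still be answered differently in front of one's own carer.
- The Discussion itself names observer bias as a limitation, which sits uneasily with the reassurance in {17a}.

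**4. Which time points are exposed?** {12} places A0 immediately after randomization, so A0 to A3 are all collected with the allocation known. The first MPI is the exception: Table 1 puts it at enrolment, and Recruitment {15} has the case manager obtain it for eligibility, before allocation.

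**5. Is the primary outcome exposed?** {12}, {18a} and {18b} take it from insurer data, and {18b} calls its collection independent of patient cooperation. The A3 question is described only as an addition. No section says how the two sources are combined.

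**The case against.** Much can be said for the protocol. Full assessor blinding is impracticable here, and the protocol says why. The Discussion discloses observer bias and plans SOPs, and evaluators are blinded. {17b} is most naturally a slip that affects no analysis. Timed up and go and DEMMI are not among the variables listed under the secondary hypotheses {7}, although the MPI is. The document does not say that control patients are assessed by different people, so the asymmetry lies in the care relationship and not in a stated difference in who asks. All of this stands. It limits the point but leaves the conflicting roles and the contradictory blinding statements in place.

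Four stronger readings are tempting, and the document does not support them.
- *That {17a} denies that any outcome needs assessor judgement.* It speaks of questionnaires only; the fault is that its argument does not reach the other measures.
- *That type I error is inflated by a known amount.* At the planning dropout, completers would be 474 × 0.5 = 237 and 474 × 0.7 ≈ 332, so the SE of a mean difference is √(1/237 + 1/332) = 0.085 SD. An assumed bias of 0.1 to 0.2 SD would be 1.18 to 2.35 SE, and a 5% test would reject about 22% to 65% of the time. Nothing in the protocol anchors that bias. The calculation also applies it to every completer and treats upper dropout allowances as expected values.
- *That the primary result is biased towards eliPfad.* No section says self-reports are added to the count. If they were, the planning dropout would let more intervention than control patients reach A3, which would tend to add events against eliPfad.
- *That using the nurse restores blinding.* The nurse would still see the tablet and devices.

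**Conclusion.** The point holds for the secondary outcomes. The protocol lets the person who delivers the intervention assess it, although it already employs someone else for assessments. It contradicts itself on assessor blinding, and its reason for discounting observer bias leaves the MPI, the mobility tests and patient response bias uncovered. The most exposed outcomes are those in which patients judge their care or burden: PACIC, treatment burden, self-efficacy and quality of life. The size of any bias cannot be derived from the document. The insurer-based primary outcome is not shown to be affected. The correction should be made, but the main analysis does not depend on it. The conclusion rests on the text alone, chiefly on reading {11a}, {11b}, {12} and {17a} together.

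**What to change.** - Assign all post-randomization assessments, A0 to A3, in both arms to the study nurse at each centre, including the A3 hospital-stay question. Leave the pre-allocation MPI screening with the case manager. Bring {11a}, {12} and {18a} into line with {5d}.
- Correct {17b} to say that only data evaluators are blinded.
- In {17a}, limit the reassurance to questionnaires and acknowledge that the mobility tests and MPI are assessed unblinded, which assigning the nurse does not cure.
- State that stays reported by patients at A3 do not add events to the insurer-based primary count.

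The cost is protocol wording and scheduling. No staff are added, but there is less flexibility when the nurse is absent.
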